### Adjuvant radiotherapy

Findings at surgery are used to determine the need for adjuvant postoperative treatment. For this study, criteria [13] (Table 2) will be reviewed in making recommendations for adjuvant radiotherapy. The delivery and management of radiation therapy will be based on local institutional clinical practice guidelines. Preliminary and final dosimetry information and concurrent administration of chemotherapy will be recorded [8].

**Table 2 Tab2:** Criteria for postoperative radiotherapy

CLS	Stromal invasion	Tumor size
Positive	Deep 1/3	Any
Positive	Middle 1/3	≥ 2cm
Positive	Superficial 1/3	≥ 5cm
Negative	Deep or middle 1/3	≥ 4cm

*CLS* Capillary lymphatic space tumor involvement

### Randomization

Patients will be randomly assigned to arm A (gasless TLRH) or arm B(TARH) in a 1:1 ratio by an internet-based distant third-party statistician blinded to the study and participant details. The doctor involved in recruitment will receive training and instructions on the recruitment procedure [18]. Only in case of a serious adverse event unblinding is permissible.

### Treatment of adverse events

Any adverse events will be managed by local investigators according to current good clinical practice guidelines. When the investigator realizes that a serious illness or other adverse events are found in the course of the clinical study, the investigator should report it to the DMC and relevant regulatory bodies as required indicating expectedness, seriousness, severity, and causality. The details of each adverse event will be described in a case report form, including the nature of the adverse event, time of onset and time of resolution, severity, treatment, and outcome. If necessary, a follow-up examination will be performed to ensure patient safety. If the physician monitoring the trial finds evidence of harm to a participant or signs of ineffectiveness, the participant will be withdrawn from the study. The results of these participants will be analyzed as a non-pCR group [18].

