### Efficacy assessments

#### The primary outcome is the rate of disease-free survival at 4.5 years

To compare disease-free survival amongst patients who undergo laparoscopic cervical cancer surgery based on open surgery versus those who undergo a total abdominal radical hysterectomy (TARH) for early-stage cervical cancer [8].

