### Statistical analysis

The main endpoint will be analyzed based on the intention-to-treat principle.

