#### Phase II analysis (phase III study)

The disease-free survival and overall survival curves will be estimated using the Kaplan–Meier method. The main comparison of survival distribution will be compared with the logrank test. The secondary analysis will use appropriate regression models (such as Cox proportional risk models) to adjust for prognostic factors. All efficacy indicators will be compared through intention-to-treat analysis, including all randomized patients. The toxicity will be analyzed based on the treatment received. The difference between treatment groups will be reported with a 95% confidence interval.

Descriptive statistics on treatment-related adverse events and quality of life (FACT-Cx, SF-12). At each evaluation, subscales (Physical Health, Social Health, Emotional Health, Functional Health, Cervical Cancer Specific Health, and Body Image Scale) will be calculated for each random group.

Similarly, descriptive statistics will be calculated for other results, such as pain score, anxiety and depression score, Analgesic consumption, etc.

The normality of continuous variables and the equality of inter-group variance will be evaluated.

Discrete variables (such as the presence/absence of postoperative infection) will be summarized as follows frequency/proportion.

For continuous variables, analysis of variance and/or regression analysis will be used where appropriate. If the assumptions of these tests are violated, alternative non-parametric tests will be used. Differences between groups with respect to discrete variables will be assessed using the chi-squared test.

Exploratory analysis adjusts prognostic factors including age, tumor size, staging, and tumor grading.

Differentiation, depth of muscle invasion, lymph node involvement, treatment type, and ECOG status will be evaluated using proportional risk regression methods. The impact of baseline quality of life on survival will also be studied.

We will analyze the results related to treatment costs based on different surgical methods [8].

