### Methods for additional analyses (e.g., subgroup analyses)

Subgroup analyses will not be conducted. However, we will apply sensitivity analysis of per-protocol analysis to assess potential biases.

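### Participants withdrawn for harm or apparent ineffectiveness are to be analysed under a response label (non-pCR) that this disease-free survival trial does not have, so their place in the primary analysis is undetermined

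*Protocol article*

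**What the plan says.** Treatment of adverse events (protocol article) sets a mandatory rule: if the monitoring physician "finds evidence of harm to a participant or signs of ineffectiveness, the participant will be withdrawn from the study". The next sentence fixes the analysis of those participants: "The results of these participants will be analyzed as a non-pCR group".

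The endpoint and analysis are described elsewhere in other terms. Under Efficacy assessments, "The primary outcome is the rate of disease-free survival at 4.5 years". Under Statistical analysis, "The main endpoint will be analyzed based on the intention-to-treat principle". Under Phase II analysis, "The disease-free survival and overall survival curves will be estimated using the Kaplan–Meier method", and "The main comparison of survival distribution will be compared with the logrank test". The same section adds: "All efficacy indicators will be compared through intention-to-treat analysis, including all randomized patients". Under Methods for additional analyses, "we will apply sensitivity analysis of per-protocol analysis to assess potential biases". The Design section states that the trial is open-label. The Discussion says that a clinical review board will assess survival and recurrence blind and independently.

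**The concern.** The rule has two parts, and each causes a problem.

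**The label.** Non-pCR belongs to a response endpoint. Here the endpoint is time to event, and nothing says how a non-pCR participant contributes to a survival curve: as an event, as a censored observation, or outside the curve altogether.

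**The withdrawal.** The participant leaves the study, and not merely a treatment. The randomised intervention is a single operation, so for someone already operated on, what remains to be left is follow-up. The trigger includes signs of ineffectiveness, which after cancer surgery plausibly means suspected recurrence, that is, a possible primary event. A physician who can know the arm makes that judgement.

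At stake is the primary comparison in the participants most likely to have an event. Until the text settles their status, the choice could be made after the data are seen, and the possible choices bias the result in different directions.

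**Working it through.** **Step 1: is pCR used anywhere else?** The primary outcome, the list of secondary outcomes, the sample size section, the statistical analysis sections and the abbreviations list were compared with the rule. pCR appears in none of them. The rule therefore cannot be applied as written.

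**Step 2: does another section repair it?** The intention-to-treat statements keep all randomised patients in the set, but do not say that withdrawn participants are still followed. The per-protocol sensitivity analysis changes who is analysed and does not recover unobserved events. Blinded review can assess what is sent to it, but the article does not say that withdrawn participants continue to supply data. None of these defines non-pCR.

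**Step 3: what each reading does.**

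- *Censored at withdrawal.* Recurrences about to be confirmed become censored times, and later deaths are lost to overall survival. The censoring is informative.
- *Counted as failure.* Someone withdrawn for surgical harm becomes a DFS failure without recurrence.

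**Step 4: size under the censoring reading (illustration).** Inputs from the Sample size section: 370 per arm, open-arm DFS 90% at 4.5 years, margin 7.2 points. That section also names other margins, which is a separate matter. Assumptions: one-sided alpha 0.025 (the article gives none), true gasless DFS exactly at the margin (90 − 7.2 = 82.8%), exponential DFS, binomial variance, and a share f of events censored at the moment they would have occurred.

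With a share f of events turned into censorings, the Kaplan–Meier estimate tends to S^(1−f). The apparent deficit is d = S_open − S_gasless, its standard error is SE = √{[S_open(1−S_open) + S_gasless(1−S_gasless)]/370}, and the chance of declaring non-inferiority is Φ((0.072 − d)/SE − 1.96).

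| Events lost | Open | Gasless | d (points) | SE (points) | Non-inferiority declared |
|---|---|---|---|---|---|
| None | 90.0% | 82.8% | 7.2 | 2.51 | 2.5% |
| 10%, gasless only | 90.0% | 0.828^0.9 = 84.4% | 5.6 | 2.45 | 9.4% |
| 10%, both arms | 0.90^0.9 = 91.0% | 84.4% | 6.6 | 2.41 | 4.5% |
| One third, both arms | 0.90^(2/3) = 93.2% | 0.828^(2/3) = 88.2% | 5.0 | 2.13 | 17.2% |
| One third, open only | 93.2% | 82.8% | 10.4 | 2.36 | under 0.1% |

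For the second row: (0.072 − 0.0562)/0.02448 = 0.644, and Φ(0.644 − 1.96) = 0.094.

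The last row shows that direction depends on where events are lost. Loss in both arms, or mainly in the gasless arm, favours a non-inferiority claim. Loss in the open arm only works against it.

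**Step 5: size under the failure reading (illustration).** Criteria for discontinuation of trial treatment mentions severe surgical complications above 3% as a trigger for evaluation. Suppose 3% of the gasless arm and none of the open arm were withdrawn for harm and coded as failures, with true DFS 90% in both arms and harm independent of recurrence. Apparent gasless DFS is 0.90 × 0.97 = 87.3%, a spurious deficit of 2.7 points. SE = √[(0.09 + 0.873 × 0.127)/370] = 2.33 points, and the chance of declaring non-inferiority is Φ((0.072 − 0.027)/0.0233 − 1.96) = 49%. Without the miscoding, SE = √(2 × 0.09/370) = 2.21 points and the chance is Φ(0.072/0.0221 − 1.96) = 90%. The 3% is used only as a scale and is not a forecast.

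**The case against.** The strongest reply is that the sentence is leftover wording. It carries a literature citation, names an endpoint used nowhere else, and should not be taken to displace two clear intention-to-treat statements. Follow-up after withdrawal and censoring rules are commonly left to the full protocol or analysis plan, which are not shown. This stands in part: silence on post-withdrawal follow-up would not by itself be a finding. But the article is not silent. It states a mandatory withdrawal and a specific analysis, and that analysis is impossible here. A fuller document could add follow-up, but could not make the non-pCR sentence valid.

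Three stronger readings are tempting and are not supported.

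- *That the rule removes participants from the intention-to-treat set.* It does not say so. Censoring and failure coding both keep every randomised patient in the assigned arm. The damage is to follow-up and event classification.
- *That lost events always pull the difference towards zero.* The open-only row of the table shows the opposite.
- *That events in withdrawn participants are certain to escape blinded review.* Nothing prevents data gathered before withdrawal from being sent to the board. The gap is that continued collection is not assured.

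Equating signs of ineffectiveness with suspected recurrence is also an interpretation, since the article does not define the term. Finally, non-pCR reads at least as naturally as failure as it does as censored. Under that reading recurrences are still counted, so the false-positive figures do not apply.

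**Conclusion.** The point holds as an error in what the article states. The rule assigns participants to a category that does not exist in this trial, makes withdrawal plausibly dependent on the primary outcome under open-label judgement, and leaves their contribution to DFS undetermined. It undermines the intention-to-treat analysis without formally contradicting who is in it.

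Confidence is high on the textual inconsistency and lower on the direction and size of bias. Under the censoring reading, false non-inferiority of about 9% (10% of gasless-arm events lost) or about 17% (one third lost in both arms), against a nominal 2.5%, shows that the effect could matter. Both figures rest on assumed loss fractions, an assumed alpha and the 7.2-point margin. Under the failure reading the bias arises from harm coded as recurrence, and it works against whichever arm has more such withdrawals.

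**What to change.** Delete the non-pCR sentence and reconcile Treatment of adverse events with the primary outcome definition, the intention-to-treat statements and the blinded review described in the Discussion. State that:

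1. participants who meet this rule remain in follow-up for recurrence and survival unless they withdraw consent to that follow-up;
2. they are analysed in the arm to which they were randomised;
3. suspected recurrence goes to the blinded review board and, if confirmed, counts as a DFS event;
4. surgical harm alone is reported under safety and is not a DFS event.

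This concerns data collection and analysis only. When a participant's treatment should be stopped is a clinical matter outside this point. The cost is a wording amendment: the follow-up visits are already in the assessment schedule, and no extra patients are needed.

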### Criteria for discontinuation of trial treatment

The criteria for the discontinuation of a trial medication are as follows:A participant declines further participation or withdraws their consent.Cancelation of the entire study.Death.The protocol treatment will be stopped if the annual patient accrual is less than 30, less than 75% of patients are available for follow-up, or an unacceptable rate of the incidence of complications (8%) occurs in the gasless TLRH group.Severe adverse events (progressive or persistent) which may be related to the surgery (such as severe surgical complications, fistula, for example, occur more than 3%) and newly diagnosed other malignancies (e.g., breast cancer, excluded transfer) will be evaluated by 2 chief physicians before the trial is stopped.Any situation in which the treatment cannot be continued according to the judgment of the physician [19].

### Discontinuation of the study

The study will be terminated early if the IRB determines the occurrence of any of the following: serious surgical complications (fistula); the participants with unexpected, significant, or unacceptable risks (such as death); the trial treatment is determined to be ineffective [19].

### Baseline assessments

Baseline assessments will be performed according to the trial standard operating procedure (SOP), including medical history, determination of BMI, CT and MRI imaging, blood tests, and cervical tissue specimens will be obtained by treating gynecologic oncologists. Histopathological examination of tissue specimens will confirm the cell type and grade of differentiation [19].

### Efficacy assessments

#### The primary outcome is the rate of disease-free survival at 4.5 years

To compare disease-free survival amongst patients who undergo laparoscopic cervical cancer surgery based on open surgery versus those who undergo a total abdominal radical hysterectomy (TARH) for early-stage cervical cancer [8].

#### Secondary outcome measures (compare between arms)

Operation time: The time from the start of the operation to the end of the operation.

Length of stay: The time from admission to discharge.

Estimated blood loss. Blood loss will be defined as the total volume of suctioned fluids minus the volumes of irrigation fluids used at the completion of surgery.

The levels of CD4^+^ T lymphocytes, NK cells, and CD4^+^ CD25^high^ CD127^low^ Treg in peripheral blood before and after operation; postoperative peritoneal immune factors IL-6, TNF-β, and TNF-α levels.

Hemodynamic parameters (cardiac output before and at the end of surgery, CO), mean arterial pressure (MAP), and stroke output (stroke volume (SV)). Pco2, blood gas analysis, ion profile.

Intraoperative complications (injury to bladder, ureters, bowel, blood vessels and bleeding, and nerves).

Perioperative complications: urinary tract infection, urinary retention, ileus, myocardial infarction, atrial fibrillation, pulmonary edema, atelectasis, pneumonia, renal and cerebrovascular morbidity, and thromboembolic complications (deep vein thrombosis, pulmonary embolism).

Early (4 weeks) postoperative complications: pulmonary, renal, and cerebrovascular morbidity; wound and vault complications (infection, breakdown, and dehiscence); septicemia and thromboembolic complications (deep vein thrombosis, pulmonary embolism); and lymphocyst or abscess formation.

Delayed postoperative complications (4 weeks–6 months after surgery): lymphedema, incisional hernia formation, vaginal evisceration.

Postoperative pain and analgesic consumption using pain scores and analgesic consumption measurements.

Costs: measured as the incremental cost/unit of improvement in functional outcome, measured in terms of the primary outcome plus using quality-adjusted life years to undertake a cost-use analysis.

The quality of life instruments(QOL) (FACT-Cx, SF12, EQ-5D, MDASI): change in QOL using functional assessment of cancer therapy-cervical between baseline (presurgery) and 6 months after surgery.

Pelvic floor distress inventory: measures symptom severity and QOL changes in women with pelvic floor disorders. The pelvic floor distress inventory provides a standardized, reproducible assessment of the patient’s symptoms and their effect on daily life.

The OS at 4.5 years follow-up [8].

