## Patients and methods

### Design

This trial is designed as an open-label, randomized phase III trial. The study protocol was approved and registered by the Ethics Committee of Shenyang Women’s and Children’s Hospital. The purpose of randomization is to eliminate selection bias. The SPIRIT reporting guidelines were used to ensure the completion of the study protocol (Additional file 1) [17]. The study flowchart is illustrated in Fig. 1.

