## Interventions

All surgeries will be performed by the same experienced surgeon. The surgeon is a chief physician with 30 years of clinical experience, proficient in minimally invasive and open surgery techniques for early cervical cancer.

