### Sample size

The main purpose of this study is to determine whether gasless laparoscopic radical hysterectomy (gasless TLRH) or equivalent to total abdominal hysterectomy (TARH) is effective in terms of disease-free survival at 4.5 years. If the difference in disease-free survival rate does not exceed 7%, then these two surgeries are considered equivalent.

The estimated 4.5-year disease-free survival rate of patients receiving TARH is 90%. The sample size was based on an expected disease-free survival rate of 90% in the open-surgery group at 4.5 years and a noninferiority margin of 7.2 percentage points for minimally invasive surgery, which reflected an acceptable difference in the expected survival rate of at most 8 percentage points. In previous studies involving patients with other types of cancer, a noninferiority margin of 6 to 8 percentage points has been considered to be clinically acceptable.

Based on these data, a total of 740 patients (370 in each group) will be sufficient to declare equivalence in 4.5 years of accrual and 4.5 years of follow-up, with an equivalence margin of 6% or less at 4.5 years [8].

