This proposed trial has strengths and weaknesses. A marked strength is that no high-quality studies are comparing the efficacy of gasless laparoscopic or abdominal surgery in the treatment of early cervical cancer. The current research experiments include ChiCTR2200064194, vaginal assisted single port laparoscopic radical surgery for cervical cancer using pneumoperitoneum and non-pneumoperitoneum: a prospective randomized controlled study. ChiCTR20000376, a randomized controlled study on the efficacy and safety of transumbilical single-hole laparoscopic surgery and traditional multi-hole laparoscopic surgery for cervical cancer. ChiCTR2100045060, a prospective randomized controlled study of robot and laparoscopic radical cervical cancer surgery. At present, there is no comparison of the clinical efficacy, safety, and clinical value between gasless laparoscopy and open surgery. If the outcome of gasless laparoscopy is the same as or better than open surgery, so this procedure had the advantages of all minimally invasive approaches, such as fast recovery and esthetic advantages. Strengths of our work also include its prospective design, standardized treatment protocol, and long duration of follow-up.

A limitation of this trial is that the design is not that of a confirmatory trial. Evaluation of the overall survival rate and recurrence rates, which are associated with the primary endpoint, will be performed by a clinical review board. The evaluation will be conducted under blind and independent conditions. And we will apply sensitivity analysis of per-protocol analysis to assess potential biases. Therefore, we believe that it will be possible to maintain objectivity and reduce potential bias. In addition, this is a single-center, randomized controlled trial design, although the operation is easy to operate and can be widely applied for gynecologists who have the foundation of traditional open cervical cancer surgery and laparoscopic surgery, in the future, we need multicenter, prospective studies to draw further strong conclusions.

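### Length of stay is counted from admission, so the between-arm comparison includes pre-operative days that the operation cannot affect: a minor, cheaply fixed weakness in one secondary outcome

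*Protocol article*

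**What the plan says.** Under Secondary outcome measures, the protocol article lists outcomes to be compared between arms and defines one of them as "Length of stay: The time from admission to discharge". Table 1 ticks length of stay in the surgery column and adds no further definition. No separate post-operative stay appears in the article.

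The Introduction and the Discussion both cite shorter hospital stay as a benefit of minimally invasive or gasless surgery over open surgery. The Discussion also expects the new procedure to have the "advantages of all minimally invasive approaches, such as fast recovery and esthetic advantages".

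On design, the article says "This trial is designed as an open-label, randomized phase III trial", and under Interventions "All surgeries will be performed by the same experienced surgeon". Under Randomization, "Patients will be randomly assigned to arm A (gasless TLRH) or arm B(TARH) in a 1:1 ratio". It does not say whether allocation comes before or after hospital admission, and it gives no admission-to-surgery interval.

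On analysis, "For continuous variables, analysis of variance and/or regression analysis will be used where appropriate", with non-parametric tests if assumptions fail, and "The difference between treatment groups will be reported with a 95% confidence interval".

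**The concern.** A between-arm comparison of stay is informative about the operation only for the part of the stay that the operation can influence. Days spent in hospital before surgery, for whatever reason, are settled before the surgical route can act. Counting them adds a component with no information on the effect of the operation.

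Two things could follow. First, if pre-operative days vary between patients, the outcome is noisier and the confidence interval wider than it need be. Second, if the mean pre-operative interval differed between arms, that difference would pass in full into the reported difference in stay and could be read as an effect of the surgery. In an open-label trial with no fixed admission-to-surgery interval the second is possible, but it is conditional.

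Other post-operative items in the article are timed from the operation: early and delayed complications, catheter days and follow-up visits. Length of stay is the exception.

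**Working it through.** The article states no mean, SD, target difference or power for length of stay, so there is no figure of its own to reproduce. What follows is an illustration of possible size.

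**Inputs from the article.** 370 patients per arm (Sample size: "a total of 740 patients (370 in each group) will be sufficient to declare equivalence"); a 95% confidence interval for the group difference; stay measured from admission.

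**Inputs assumed.** Post-operative SD of 3 days (range 2 to 4); pre-operative SD of 0.5 to 3 days; pre- and post-operative days independent. None of these is in the article.

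**Precision.** Total stay is pre-operative plus post-operative days, so under independence:

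- SD_total = √(SD_post² + SD_pre²)
- variance ratio = (SD_post² + SD_pre²) / SD_post²
- 95% half-width of the difference in means = 1.96 × SD_total × √(2/370)

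Example with SD_post = 3 and SD_pre = 2: variance 9 + 4 = 13, ratio 13/9 = 1.44, SD_total = 3.61, half-width 1.96 × 3.61 × √(2/370) = 0.52 days. With the pre-operative days removed: 1.96 × 3 × √(2/370) = 0.43 days.

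The full set at SD_post = 3, with power for a true difference in post-operative stay at two-sided 5%:

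| Pre-operative SD (days) | SD of total stay | Variance ratio | 95% half-width (days) | Power, true difference 0.5 day | Power, true difference 1 day |
|---|---|---|---|---|---|
| 0 (clock starts at surgery) | 3.00 | 1.00 | 0.43 | 62.1% | 99.5% |
| 0.5 | 3.04 | 1.03 | 0.44 | 60.9% | 99.4% |
| 1 | 3.16 | 1.11 | 0.46 | 57.6% | 99.0% |
| 2 | 3.61 | 1.44 | 0.52 | 47.1% | 96.5% |
| 3 | 4.24 | 2.00 | 0.61 | 36.1% | 89.4% |

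Over the wider grid (SD_post 2 to 4, SD_pre 0.5 to 3) the variance ratio runs from 1.02 to 3.25. The half-width goes from 0.29–0.58 days to 0.30–0.72 days.

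**Location.** Expected difference in total stay = expected difference in post-operative stay + expected difference in pre-operative stay. If the last term is zero, the comparison of means is unbiased and only precision is lost. If it is not zero, it enters one for one. The article gives nothing from which to put a number on it.

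**The case against.** The case on the other side is substantial. Admission to discharge is a complete and unambiguous definition of hospital stay, and it suits the cost outcome in the same list. The article contains no error or contradiction here. The outcome list does not say that stay is meant as a recovery measure. The Introduction names shorter stay and faster functional recovery as separate items, and pain, analgesic use, quality of life and complications are measured in their own right. All the SDs above are assumed, and even a pre-operative SD of 2 days leaves 96.5% power for a 1-day difference. Post-operative stay could be derived later from dates already held.

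Most of this stands, and it limits the point to a minor one. It does not remove it. The article itself presents shorter stay as a benefit of the surgical route, yet the one definition it fixes for the between-arm comparison includes time before the surgery.

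A reader might go further and infer that the open-label design lets scheduling differ by arm, so that the comparison is biased. The documents do not support that. They describe no arm-specific scheduling. The abdominal-wall suspension and the vaginal closure, which might be thought to delay the laparoscopic cases, are described under Interventions as steps of the operation, the vaginal closure after anesthesia. Nothing ties either to waiting days. One surgeon at one center operates on both arms, which if anything makes a systematic difference in waiting less likely. Bias remains a possibility that the definition leaves open.

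**Conclusion.** The point holds as a small weakness in one secondary outcome. The definition counts pre-operative days that the operation cannot affect. This can widen the interval for the arm difference, and it would shift that difference only if admission-to-surgery time happened to differ by arm, which is not shown.

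The size cannot be established from the documents. At an assumed post-operative SD of 3 days it ranges from about 3% extra variance, which is negligible, to 100% if pre-operative stay varies as much as post-operative stay. These figures also assume independence: a positive correlation between the two parts would raise them and a negative one would lower them.

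The primary outcome, disease-free survival at 4.5 years, and the sample size of 740 do not depend on this.

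**What to change.** Define post-operative stay, from the date of surgery to discharge, as the between-arm comparison of stay. Keep admission to discharge as a resource-use measure for the cost analysis, where the whole stay is the relevant quantity.

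The cost is one line of wording and one extra derived variable. No new data should be needed: the follow-up visits are timed from surgery, so its date must already be held, and the discharge date is part of the present definition. A patient randomized but never operated on would have no value, so the wording should say how such cases are handled. The change is best made before any comparison between arms has been seen.
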